## Methods

### Overview

Participants will be randomly assigned to an aerobic exercise group, an HIIT group, or a control group. Participants in the first 2 groups will partake in a 10-week training program, conducted 3 times per week on nonconsecutive days. Participants in the control group will participate in other physical activities during the same intervention period.

### Study Design

A randomized controlled trial will be used to examine the effects in individuals who are assigned to either a 10-week aerobic exercise training group, a 10-week HIIT training group, or a control group. A total of 78 secondary school adolescents will be recruited for this study. Subsequently, the adolescents will be randomly clustered in a controlled intervention trial. The effectiveness of the intervention will be assessed through a pretest, posttest, and a follow-up design that will be evaluated based on the degree of improvement in performance across the 3 time points. If any important protocol modifications are made, all relevant parties will be informed. These include the trial registry, human research ethics committee, research team members, all participating students and their parents, the journal that publishes the study protocol, and the funding body.

### Participants

G*Power [47] was used to estimate the sample size based on analysis of variance (ANOVA) with Cohen *f* [48] medium effect size set as 0.25 and Cronbach α, as .05. A total of 45 participants are required to achieve sufficient statistical power. Assuming a 20% attrition rate [49] and clustering effect (assumed as 0.01) [50], the principal investigator (PI) will gather a total of 78 participants aged between 12 and 15 years from 3 to 4 secondary schools in Hong Kong. Each group will comprise 33% (26/78) of participants.

We will conduct the study across 3 to 4 secondary schools that will be randomly selected. Students will be invited to participate in the study given that they (1) are aged between 12 and 15 years and (2) belong to a family with a household income below half of the median household income reported in Hong Kong, which is adjusted by household size. These selection criteria are based on a study by Costigan et al [8], which examined the effect of HIIT on cognitive and mental health among adolescents. Participants (1) with hypertension or diabetes mellitus without control; (2) with a history of brain injury and other neurological diseases, epilepsy, or myocardial infarction; (3) with recent musculoskeletal disease; (4) who use medication that affects HR (eg, *β*-blockers, asthma medications, stimulants, digoxin, and antiarrhythmic agents); or (5) with cardiovascular disease will be excluded from this study. All participants in the exercise groups must complete a Chinese version of the Physical Activity Readiness Questionnaire for a safe preliminary screening before the exercise class [51].

### Procedures

After obtaining ethical approval from the institution, the author will contact the principals of the selected secondary schools to seek their permission to recruit participants from the pool of students. A research assistant will obtain informed consent forms and the Physical Activity Readiness Questionnaires from the participating students and their parents. Before the intervention, the students will be asked to complete the baseline assessment for the exercise programs. They will be asked to perform the assessment again after completing the exercise programs. A cluster design will be used for all the participants in the same school to delegate them to the same combination of 2 intervention groups and a control group. The participants will be randomly assigned to 1 of the 3 groups. The trial is designed to simultaneously evaluate the impact of the 2 interventions. Randomization will be performed using computer-generated random numbers by a trained research assistant blinded to the identities of the participants. The research assistant conducting the randomization will not be involved in any data collection. The entire process of data collection and intervention will be conducted by other trained research assistants who are blinded to the participants’ group assignments. A follow-up assessment will be conducted 3 months after the exercise program to examine the long-term effects of such an intervention. All assessments will last for 45 minutes. All participants will be given an exercise diary or logbook to keep track of their exercise habits (ie, record the type of exercise or activity, hours, and intensity of exercise or activity every day) throughout this study (Figure 1).

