### Data Analysis

Interim analysis will not be performed, and data analysis will only begin after the follow-up stage. The PI and trained research assistants will have access to the final trial data set. Data will be analyzed using SPSS version 26. A missing value analysis procedure will be conducted to detect the missing values in the data file. The demographic characteristics of the participants will be investigated using the chi-square test for independence (for nominal variables) and 1-way ANOVA (for continuous variables). A Bonferroni post hoc test will subsequently be conducted for group comparisons. To examine the changes between and within groups for each outcome measure (ie, self-efficacy, mood, enjoyment, working memory, cognitive flexibility, inhibition, depression, anxiety, and stress), a 3 (before intervention vs after intervention vs follow-up) × 3 (aerobic exercise vs HIIT vs control) repeated-measure ANOVA will be conducted. A post hoc analysis will be used to confirm whether significant differences for any of the outcome variables exist among the groups. The Bonferroni method will be used to adjust the *P* values.

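### The article describes both clustered and individual randomisation, and the outcome model has no school or training-group term although the sample size allows for clustering

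*Protocol article*

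**What the plan says.** The unit of assignment is described in four places in the protocol article.

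- Study Design says the trial is designed "to examine the effects in individuals who are assigned to either a 10-week aerobic exercise training group", which is individual assignment. Two sentences later, "the adolescents will be randomly clustered in a controlled intervention trial", with no cluster defined.
- Procedures says "A cluster design will be used for all the participants in the same school", and the sentence goes on to send them to one and the same set of two exercise groups plus control. The next sentence is individual again: "The participants will be randomly assigned to 1 of the 3 groups".

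The Participants section raises a requirement of 45 to 78 for 20% attrition and a "clustering effect (assumed as 0.01"), recruited from 3 to 4 schools with 26 per arm.

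The Data Analysis section fixes the model for each outcome: a 3 (time) by 3 ("aerobic exercise vs HIIT vs control) repeated-measure ANOVA will be conducted", followed by Bonferroni-adjusted post hoc tests. No school or training-group term appears.

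The exercise is delivered to groups. The aerobic and HIIT sections describe trainer-led sessions, and the adherence section adds partner work and a peer-support and reward system. The number of exercise classes per arm is not given.

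**The concern.** The unit of randomisation decides which analysis is valid, so a protocol should give one answer to it. Here the text uses both clustered and individual language. The sample size also treats outcomes as correlated, while the stated analysis treats all participants as independent. Because the model is written out, this is a mismatch between two stated parts of the plan, not a detail left to a later document.

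Two kinds of correlation could matter, and they act in opposite directions. Correlation within school matters little if every school feeds all three arms. Correlation within a shared exercise class belongs to one arm only and would make the standard error of an arm comparison too small, including the comparison of aerobic exercise with HIIT that the second research question asks for.

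**Working it through.** **1. Which unit does the text support?** The Procedures sentence gives each school the same set of three groups, so no school is confined to one arm. Individual assignment is stated in Study Design and in Procedures, and equal arms of 26 are natural if individuals are allocated. The consistent reading is individual randomisation within school, with school as a stratum.

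**2. Is clustering really in the sample size?** Attrition alone gives 45 / 0.8 = 56.25, so 57. The plan has 78, which is 21 more. With schools as clusters, m = 78/4 = 19.5 to 78/3 = 26, and the design effect 1 + (m − 1) × 0.01 is 1.185 to 1.25. That gives 45 × 1.185 / 0.8 = 66.7 to 45 × 1.25 / 0.8 = 70.3. This does not reproduce 78, which is a separate matter. For this point it is enough that 78 exceeds the attrition-only figure and that the text names a clustering allowance.

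**3. Setting for the error rates.** I simplify to one score per participant and compare arm means while ignoring clusters. Let ρ be the ICC of the score or change being tested, k the number of groups per arm, n the group size and N = kn. In units of the total variance, the expected within-arm sample variance is

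E(s²) = (1 − ρ) + ρ × [N/(N − 1)] × [(k − 1)/k].

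Take k = 3 and n = 9, so N = 27, close to 26. Then E(s²) = 0.99 + 0.01 × (27/26) × (2/3) = 0.9969 at ρ = 0.01, and 0.9692 at ρ = 0.10.

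**4. School omitted, individuals randomised within school.** School effects are shared by the arms and cancel from their difference, so the true variance factor is 1 − ρ.

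- ρ = 0.01: ratio of true to assumed variance = 0.99/0.9969 = 0.993. The F critical value is 3.114 (2 and 78 df), and P(F > 3.114/0.993) = 4.9%. A simulation of 20,000 runs gave about 4.7%, and one of 100,000 runs gave 4.9%.
- ρ = 0.10 (assumed): ratio 0.90/0.9692 = 0.929, giving 4.0%. Simulations gave 4.0% to 4.2%.

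The standard error is too large by √(1/0.993) − 1 = 0.4% at 0.01, and by √(1/0.929) − 1 = 3.8% at 0.10. That is a small loss of precision and produces no excess of false positives.

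**5. Training groups ignored.** A class belongs to one arm, so its effect does not cancel, and the true variance factor is 1 + (n − 1)ρ.

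- ρ = 0.01, n = 9: (1 + 8 × 0.01)/0.9969 = 1.083. P(F > 3.114/1.083) = 6.2% for the three-arm test. For aerobic against HIIT, P(|t| > 2.007/√1.083) = 5.9% on 52 df.

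Simulated error rates with 3 to 4 classes per arm (assumed), nominal 5%:

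| ICC | Aerobic vs HIIT t test | Three-arm F test, groups in all arms |
|---|---|---|
| 0.01 (the plan's value) | 5.7–6.0% | about 6% |
| 0.05 (assumed) | 8–10% | 10–12% |
| 0.10 (assumed) | 11–15% | 16–19% |

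These are error rates of a simplified test, not of the full repeated-measures ANOVA. A school effect that is constant over time drops out of the time-by-arm interaction altogether, so ρ here has to be read as the correlation in the contrast being tested.

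**The case against.** The best defence is that the cluster wording is loose and no more. The Procedures sentence read to its end gives every school all three arms, and the sentence after it randomises participants. On that reading, leaving school out does no harm to the error rate. At the only clustering value in the document, the class effect moves the error by about one percentage point. The larger figures need ICCs and class counts that the article does not contain. Nearly all of this stands, and it limits the point to one of clarity and consistency. It does not answer the mismatch itself: the plan allows for clustering in its size and then states a model without it, and a reader still has to infer the unit.

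Two stronger readings are tempting. A reader might infer from the cluster wording that whole schools are allocated. Between-school degrees of freedom would then be 3 − 3 = 0 or 4 − 3 = 1, and the arms could hardly be compared. The text does not support this, because no school is said to receive a single arm. A reader might also infer that randomisation is unblocked and unstratified. The article says only that computer-generated random numbers are used. That is silence on a detail which a journal article commonly leaves to the full protocol.

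The defence is also right that a compulsory class effect would be costly. With 3 to 4 classes in each of two arms, a test on between-class variation has 2 × (3 − 1) = 4 to 2 × (4 − 1) = 6 degrees of freedom, with critical t of 2.78 to 2.45 against about 2.01. From the critical value alone, intervals widen by 2.45/2.01 − 1 = 22% to 2.78/2.01 − 1 = 38%. With one class per arm, class cannot be separated from arm at all.

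**Conclusion.** The point holds as an inconsistency that should be fixed. The unit of randomisation is worded in two ways, and the clustering allowed for in the sample size is missing from the stated model. The text supports individual randomisation within school. On that reading, omitting school gives an error rate of about 4% to 4.9%, which is conservative and costs a little precision. Ignoring shared training groups gives about 6% at the plan's own 0.01. It would give roughly 8% to 19% only at assumed ICCs of 0.05 to 0.10, across the two tests tabulated. These figures rest on an assumed 3 to 4 equal classes per arm and one score per participant. The documents do not show a trial that cannot be analysed.

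**What to change.** - **Design wording.** Replace the cluster wording in Study Design and Procedures with one statement: individual participants are randomised 1:1:1 within each school, with school as a stratum. This should be settled before allocation.
- **Main model.** Add school as a fixed effect in every outcome model. In the repeated-measures model, let it also interact with time, so that it bears on the time-by-arm test. The cost is 2 or 3 between-participant degrees of freedom for 3 or 4 schools, and twice that number within participants.
- **Training groups.** State the number of exercise classes and trainers per arm. Where an arm has several classes, report a sensitivity analysis with a class effect in the exercise arms (partially nested model, small-sample degrees of freedom). Where there is one class per arm, state that class and arm effects cannot be separated. The cost is wider intervals, confined to the sensitivity analysis.

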**Figure 1 figure1:**
[figure not shown]
Flow diagram: study design and data collection procedures. HIIT: high-intensity interval training; HR: heart rate.

### Aerobic Exercise Group

Following the exercise recommendation in the literature review and the study by Ranjbar et al [37], this study will conduct the aerobic exercise classes over a period of 10 weeks. The participants will complete 3 training sessions per week. In addition, each aerobic training program will last for 1 hour. The session will include a 10-minute warm-up period, followed by a 45-minute aerobic workout, wherein the participants can choose to use either a treadmill, a cycle ergometer, or a rowing ergometer. After the workout, a 5-minute period of stretching will be provided for cooling down. The intensity during the workout will be set at 40%-55% of the individual’s maximum HR [37].

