### Exercise Regimen

Although a lack of consensus regarding the most effective training regimen for physical exercise is evident in clinical review studies from 2000 to 2014, Ranjbar et al [37] have recommended the following components of an effective exercise program to benefit adolescents with poor mental health. On the basis of the frequency, intensity, time, and type principle, an exercise program should include the following characteristics: (1) structured aerobic exercise, which requires the heart to pump oxygenated blood for delivering oxygen to working muscles and stimulates an increase in the heart rate (HR) and breathing rate [38]; (2) group exercise, particularly for adolescents; (3) low (40%-55% maximal oxygen consumption) to moderate (65%-75% maximal oxygen consumption) intensity exercise; (4) 45- to 60-minute exercise sessions; (5) exercise frequency of at least three to four sessions per week, which is equal to ≥150 minutes of exercise per week; and (6) an exercise duration equal to ≥10 weeks.

Overall, extensive research has confirmed that physical exercise can significantly improve physical and mental health, whereas aerobic exercise has been the main focus of most previous studies. Recent studies have attempted to determine whether low-volume high-intensity interval training (HIIT) could be a time-efficient exercise strategy for improving health and fitness among the general population.

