### Research Gaps and Study Objectives

The conditions and ability of poor individuals to manage and potentially escape poverty are the core of policy agendas and ethical and economic concerns among societies. Behavioral research has recently been applied to policy-relevant challenges and has explored the significant potential of simple interventions to influence cognition and behavior [45]. Poor individuals, particularly young poor individuals in Hong Kong, have received little attention as part of this endeavor despite their characteristics that satisfy the qualifications of clear candidates for interventions that could improve disadvantaged situations.

Although several longitudinal studies have confirmed that growing up in a disadvantaged family is a significant risk factor for poor mental health, numerous research gaps should be addressed by further investigation. For instance, most studies on mental health and socioeconomically disadvantaged adolescents have been restricted to understanding and confirming the link between mental health and SES. Research that aims to examine whether mental health can be enhanced through physical exercise is scarce. However, such research would be extremely useful for expanding early interventions. To date, a steady decline in the number of physically active students in Hong Kong is evident. Furthermore, the situation among adolescents in Hong Kong is worse, given that 96% of them are insufficiently active [46]. Hence, there is a considerable need for this kind of research to arouse public awareness of the link between physical activity and mental health. Although previous studies have reported improvements in the mental health of adolescents after exercise sessions, a lack of follow-up data is available on assessing the sustainability of exercise intervention with moderate intensity over a long duration. In addition, relatively few studies have directly compared the effects of aerobic exercise and HIIT on the mental health of adolescents with low SES. Given that HIIT training has become popular and effective in improving health and well-being, HIIT exercise should be used as the comparison group to examine the effectiveness of traditional aerobic exercise.

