Following the health benefits of regular exercise and the limited research on exercise-based interventions (aerobic exercise vs HIIT) in low-SES adolescents, this study primarily aims to investigate the effectiveness of aerobic exercise and HIIT on the 3 indicators of mental health among low-SES adolescents. This study particularly intends to answer the following two research questions: (1) Is there any change in the 3 indicators of mental health (ie, cognitive function, well-being, and ill-being) before and after exercise? and (2) Which exercise regimen (aerobic exercise or HIIT) is more effective in reducing ill-being and enhancing well-being and cognitive function among adolescents with low SES?

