### HR Monitoring

To monitor the intensity of the training during the program, the participants are required to wear HR monitor watches (Polar Electro Oy). The recorded HR data will be uploaded to a computer and will be checked regularly by investigators to determine whether the participants could reach the target HR during the exercise. Furthermore, the length of time (number of minutes and average session duration) when the participant reaches the HR targets will be recorded. The participants will also be encouraged to achieve the target HR during the session. The maximum HR will be calculated according to the age-based formula (220-age). To ensure their safety and manage unexpected situations, a subjective measurement of physical exertion (using Borg scale 6-20) will also be monitored during every training session by an assistant trainer [56].

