### Physiological Outcome Measures

The physical health outcomes survey will include measures of blood pressure (BP), resting HR, body weight (BW), height, waist circumference (WC), and hip circumference (HC). BP will be measured using an automated BP monitoring device. The participants will be given a 10-minute rest before the measurement. The BP will be measured twice, with a 1-minute interval between the readings. Additional readings will be obtained if the BP measurements differ by >5 mmHg. The mean of the 3 consecutive readings will be used as the examination value. The resting HR will be measured through a wireless HR monitor that will be worn by the participants (Polar Electro Oy) for 1 minute after their 10-minute rest. BW and height will be measured using an electronic digital scale and a stadiometer, respectively. BMI will be calculated by dividing BW (kg) by height (m^2^). The WC and HC measurements will be adopted from the study by Bacopoulou et al [69]. The WC and HC will be measured twice using an anthropometric tape while the adolescents stand erect and relaxed with their arms at their sides and feet positioned close together. The WC will be measured between the upper border of the iliac crest and the lowest border of the rib cage at the end of normal expiration. The HC will be measured at the widest part of the hip at the level of the greatest trochanter. For all the measurements, the tape will be positioned at a level that is parallel to the floor. Furthermore, the unit of measure will be in centimeters to the nearest 0.1 centimeter. The waist-to-hip ratio will be calculated as the ratio of the waist-to-hip circumference. All physical data will be recorded in the resting state at the baseline each week and at the end of training. The measurement for the physical health outcome assessment will be performed by a trained research assistant.

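### The aerobic target is 40%-55% of maximum heart rate, but the recommendation it claims to follow is reported as 40%-55% of maximal oxygen consumption

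*Protocol article*

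**What the plan says.** In the protocol article, the Exercise Regimen section lists the components of an effective programme recommended by source [37]. The intensity component reads "low (40%-55% maximal oxygen consumption) to moderate (65%-75% maximal oxygen consumption) intensity exercise", so both bands are on the oxygen-consumption scale.

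The Aerobic Exercise Group section presents the arm as built on that list ("Following the exercise recommendation in the literature review", together with source [37]). It then sets the dose: "The intensity during the workout will be set at 40%-55% of the individual’s maximum HR [37"]. The programme length (10 weeks), the frequency (3 sessions a week) and the 1-hour session with a 45-minute workout also follow the list. Only the intensity changes scale.

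The HR Monitoring section puts the HR figure into use. It states "The maximum HR will be calculated according to the age-based formula (220-age"), has investigators check whether participants reach the target, and specifies that the length of time "when the participant reaches the HR targets will be recorded".

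The textbox in the HIIT Group section sets active recovery between work bouts at 40%-50% of maximum HR.

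**The concern.** A percentage of maximal oxygen consumption and the same percentage of maximum HR are different quantities. When one source is cited for the same two numbers on both scales, with no conversion, at least one statement of the recommendation is wrong or unexplained. The figures look carried across rather than converted, though that is an inference.

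The affected figure is the dose of one randomised arm. The second research question asks "Which exercise regimen (aerobic exercise or HIIT) is more effective in reducing ill-being" and enhancing well-being and cognitive function. If the aerobic arm runs at a lower intensity than the recommendation it claims to implement, a null aerobic result or an advantage for HIIT could not be read as evidence about the recommended regimen. It would be evidence only about the lower dose delivered. Once training has started, no analysis can recover the intended dose.

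**Working it through.** **Step 1: the two statements side by side.**

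| Section | Source | Band | Scale |
|---|---|---|---|
| Exercise Regimen | [37] | 40%-55% (low) | maximal oxygen consumption |
| Aerobic Exercise Group | [37] | 40%-55% | maximum HR |

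No other section reconciles them. This mismatch needs no arithmetic and no outside knowledge.

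**Step 2: the written target in bpm, from the documents alone.** Ages are 12-15 years (Participants section) and maximum HR is 220 minus age.
- Age 12: maximum 220 - 12 = 208; band 0.40 × 208 = 83.2 to 0.55 × 208 = 114.4 bpm.
- Age 15: maximum 220 - 15 = 205; band 0.40 × 205 = 82.0 to 0.55 × 205 = 112.75 bpm.

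Across the age range the written target is 82-114 bpm.

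**Step 3: comparison with HIIT active recovery, from the documents alone.** The recovery band of 40%-50% of maximum HR is 83.2-104.0 bpm at age 12 and 82.0-102.5 bpm at age 15. It lies wholly inside the aerobic work band and covers 10 of its 15 percentage points.

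**Step 4: illustration if the oxygen-consumption scale is the right one.** The documents give no conversion. Assume that percent oxygen consumption is roughly percent HR reserve, and take resting HR of 60 and 90 bpm. Neither assumption is in the documents. The limit is rest + p × (maximum - rest), with p = 0.40 or 0.55.

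| Resting HR | Age | Lower limit (bpm) | Upper limit (bpm) |
|---|---|---|---|
| 60 | 12 | 60 + 0.40 × 148 = 119.2 | 60 + 0.55 × 148 = 141.4 |
| 60 | 15 | 60 + 0.40 × 145 = 118.0 | 60 + 0.55 × 145 = 139.75 |
| 90 | 12 | 90 + 0.40 × 118 = 137.2 | 90 + 0.55 × 118 = 154.9 |
| 90 | 15 | 90 + 0.40 × 115 = 136.0 | 90 + 0.55 × 115 = 153.25 |

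The target would be about 118-141 bpm at resting HR 60 and 136-155 bpm at resting HR 90. The two rows should not be merged into one wide band, because no participant would have it.

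The shortfall of each written limit is (1 - p) × rest. For the lower limit it is 0.60 × 60 = 36 to 0.60 × 90 = 54 bpm. For the upper limit it is 0.45 × 60 = 27 to 0.45 × 90 = 40.5 bpm.

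**Step 5: how far this depends on the conversion.** Suppose the conversion is off by 10 percentage points of HR reserve in either direction.
- The smallest shortfalls occur at resting HR 60, maximum 208, shift -10: lower limit 36 - 14.8 = 21.2 bpm, upper limit 27 - 14.8 = 12.2 bpm.
- The largest occur at resting HR 90, maximum 208, shift +10: lower limit 54 + 11.8 = 65.8 bpm, upper limit 40.5 + 11.8 = 52.3 bpm.
- At resting HR 60 and maximum 208, the limits would coincide only if the conversion were off by 27/148 = 18.2 points (upper) or 36/148 = 24.3 points (lower).

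The direction is therefore stable within this range, but the size is not.

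**The case against.** The strongest reply is that the fault cannot be located. Source [37] is not available, and the slip may sit in the background section. In that case a unit is wrong in the literature review and conduct does not change. This stands, and it makes the harm conditional. It does not remove the contradiction, because one of the two sections needs correcting either way.

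A second reply is that low intensity is a legitimate choice and that HR is a practical way to steer sessions. Both are true and neither is disputed. The High-Intensity Interval Training section itself contrasts HIIT with low-intensity, high-volume endurance training, so a low-intensity comparator fits the article's framing.

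A third reply is that HR is not the only control on delivery. The arm has a fixed 45-minute machine workout, a certified trainer, and exertion ratings on the Borg scale every session. This is fair. A participant with a resting HR of about 82-83 bpm would meet the bottom of the band without exercising, but that concerns only the lower edge, and the number of such participants is unknown.

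Four stronger readings are tempting and go too far:
- **That the aerobic arm is certainly under-dosed.** This needs the Exercise Regimen section to be right, and it needs a conversion that the documents do not supply.
- **That the article equates the source [37] regimen with traditional aerobic exercise.** The Research Gaps and Study Objectives section says "HIIT exercise should be used as the comparison group to examine the effectiveness of traditional aerobic exercise", but it cites neither source [37] nor an intensity band there.
- **That the written and intended bands do not overlap.** With the 10-point shifts, the intended floor minus the written ceiling runs from 104.4 - 114.4 = -10.0 bpm (resting HR 60, maximum 208, shift -10) to 147.5 - 112.75 = +34.75 bpm (resting HR 90, maximum 205, shift +10), so overlap is unsettled.
- **That the outcome analysis is biased.** Time at target is a monitoring record. The Data Analysis section uses it neither as an outcome nor to define an analysis set.

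**Conclusion.** The concern holds as an internal contradiction in a figure the trial runs on. Confidence is high that the two sections disagree and moderate that harm follows.

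From the documents alone, the operative target is 82-114 bpm and contains the whole HIIT recovery band. If the Exercise Regimen section has the right scale, the written limits are about 36-54 bpm (lower) and 27-41 bpm (upper) too low under the HR-reserve assumption at resting HR 60-90. The aerobic arm would then be under-dosed relative to its stated basis, and conclusions about the recommended regimen would be unsupported. If the Aerobic Exercise Group section is right, only a unit and the description of the arm need correcting.

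In either case the randomised comparison of the regimens as delivered remains valid. What is at risk is what the aerobic result can be said to be about. This should be fixed before training begins.

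**What to change.** Before the first session, check the scale in source [37] and make the Exercise Regimen and Aerobic Exercise Group sections agree.

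- **If the oxygen-consumption scale is right:** replace the aerobic target with an HR equivalent chosen by the exercise team, for example 40%-55% of HR reserve. Use the baseline value already planned in the Physiological Outcome Measures section ("The resting HR will be measured through a wireless HR monitor"), and record time at target against the new band.
- **If the maximum-HR scale is right:** correct the unit in the Exercise Regimen section and describe the arm as low-intensity aerobic exercise in the conclusions.

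The cost is a text correction and, if the target changes, individual HR targets and a trainer briefing. Resting HR is already measured, so no extra visit or equipment is needed.
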